## Abstract

**Background:**

Dose-escalated radiotherapy is known to improve progression free survival in patients with localized prostate cancer, and recent advances have led to the standardization of ultrahypofractionated stereotactic ablative radiotherapy (SABR) delivered in just 5-fractions. Based on the known effectiveness of the accepted though invasive 2-fraction treatment method of high-dose-rate brachytherapy and given the ubiquity of prostate cancer, a further reduction in the number of treatments of external-beam SABR is possible. This study aims to evaluate the safety, efficacy, and non-inferiority of generalizable 2-fraction SABR compared to the current 5-fraction regimen.

**Methods:**

502 patients will be enrolled on this phase II/III randomized control trial. Eligible patients will have previously untreated low- or favorable intermediate-risk adenocarcinoma of the prostate. Patients will be randomized between standard SABR of 40 Gy in 5 fractions given every-other-day and 27 Gy in 2 fractions at least two days apart but completing within seven days. MRI-based planning, radiopaque hydrogel spacer insertion, and fiducial marker placement are required, and SABR will be delivered on either a standard CT-guided linear accelerator or MR-LINAC. The primary endpoint will be freedom from disease progression, with additional secondary clinical, toxicity, and quality of life endpoints.

**Discussion:**

This study will be the largest prospective randomized trial, adequately powered to demonstrate non-inferiority, comparing 2-fraction SABR to standard 5-fraction SABR for localized prostate cancer. As the protocol does not obligate use of an MRI-LINAC or other adaptive technologies, results will be broadly generalizable to the wider community.

**Trial registration:**

This trial is registered on Clinicaltrials.gov: ClinicalTrials.gov Identifier: NCT06027892.

## Background

Following publication of multiple prospective clinical trials demonstrating the biochemical progression free survival (bPFS) benefits, and possible metastasis-free and cancer-specific survival, of high dose radiation for the curative treatment of localized prostate cancer, typical external beam radiotherapy (EBRT) courses ranged from 38 to 45 daily fractions delivered over 7.5-9 weeks [1–5]. In recent years monumental advances in EBRT have been achieved, allowing significant shortening of the standard radiotherapy course [6–8], and together with diagnostic and technological developments, ultrahypofractionated regimen in the form of stereotactic ablative radiation therapy (SABR) is now an accepted standard of care for definitive treatment in the low- and favorable intermediate-risk settings [9].

At both the individual and systems levels, efficient delivery of patient care and prudent utilization of medical resources is at the forefront. Given the ubiquity of prostate cancer and high patient volumes worldwide, there remains meaningful potential for improvements in patient throughput and cost of care. Presently, the shortest treatment courses for low- and favorable intermediate-risk prostate cancer are radical prostatectomy and low-dose-rate (LDR) brachytherapy, which offer an excellent likelihood of cure [10–11] but are invasive procedures that may not be appropriate, feasible, or desirable for all patients, and include additional costs associated with operating room facilities and anesthesia. A comparable radiation therapy treatment course would help address many of these concerns in patient care.

A strong and mature precedent for a two-fraction course of high dose radiation can be found in the realm of high-dose-rate (HDR) brachytherapy. Under anesthesia, a radioactive source is programmed to traverse catheters that have been transperineally inserted into the prostate in order to produce a desired dose. bPFS rates range between 91 and 97% in the modern literature [12]. While attempts were made to deliver single-fraction HDR brachytherapy, trials consistently revealed the need for two fractions/procedures in the definitive setting [13]. While LDR brachytherapy is technically a single procedure of radiation delivery, the gradual decay of the standard radioisotopes (I-125, Pd-103, Cs-131) over weeks to months is more akin to extreme hyperfractionation over time which may contribute to prolonged toxicity.

There exists, to date, limited data on the safety and effectiveness of prostate SABR delivered in fewer than five fractions. A recent proof-of-concept study by Greco et al. compared single-dose SABR of 24 Gy to 5 fractions of 9 Gy in favorable intermediate and unfavorable intermediate risk patients [14]. They utilized an air-filled rectal balloon to limit rectal motion and planned with no posterior planning target margin. The results demonstrated comparable four-year PSA outcomes for favorable intermediate disease though inferior PFS for unfavorable intermediate disease. Objective and patient reported GU and GI toxicities were not significantly different, though one of the 15 patients in the single-fraction arm experienced delayed grade 3 urethral stenosis. Magli et al. published acceptable 1-year toxicity outcomes for a novel three-fraction regimen of SABR for low- and favorable intermediate-risk patients, to a dose of 40 Gy. MRI-based planning was utilized, gold fiducials and a hydrogel spacer were placed, and a catheter was inserted in the bladder for each fraction [15]. They observed rates of 11.9% and 1.7% acute grade 2 and 3 urinary toxicity, respectively, and 8.5% acute grade 2 rectal toxicity, all of which resolved by 12 months. Alayed et al. published safety and efficacy results of their prospective single-cohort study of low- and intermediate-risk patients undergoing a two-fraction SABR regimen to a dose of 26 Gy [16]. Radiation was delivered to the prostate alone using a 3 mm uniform expansion. The study was performed prior to development and standardization of peri-rectal hydrogel spacers. On their sample of 30 patients, they reported no acute grade 3 + GI or GU toxicity, and one instance each in later follow up, comparable or even slightly better than that from five-fraction protocols. An additional phase-II study has begun accruing of five vs. two fractions of SABR for low- and intermediate-risk prostate cancer (ClinicalTrials.gov identifier: NCT04984343), though requiring MRI-based adaptive therapy technology and utilizing lower radiation doses.

Multiple questions remain regarding the potential role for SABR in fewer than five fractions. These include optimal patient selection, ideal dose fractionation, proper techniques to assure necessary avoidance of surrounding normal tissue, and how to balance dose to organs at risk with the accepted requirement of a planning target volume (PTV) to account for inevitable setup uncertainty. Importantly, recent endoscopic reports reveal notably high rates of rectal ulceration after dose-escalated SABR [17], and placement of a hydrogel spacer has been demonstrated to significantly reduce this risk [18]. Placement of a resorbable hydrogel spacer to displace the rectum away from the high dose region, allowing for a posterior safety margin to account for potential intra-fractional motion, instead of a rectal balloon, is essential for accomplishing rectal sparing while facilitating additional assurance regarding treatment accuracy. A degree of posterior planning margin importantly helps assure adequate coverage of the posterior aspect of the prostate, coverage of which has been shows to correlate directly with tumor marker recurrence [19].

In the context of modern dose escalation, and in lieu of a strong body of HDR-brachytherapy data supporting a two-fraction approach to ultra-high dose treatment with initial experiences of two-fraction SABR, direct comparison of a non-invasive and broadly generalizable two-fraction SABR regimen to the standard approach of five-fractions is logical. Institutional studies have emerged in the recent years demonstrating evidence for safety of ultra-hypofractionated regimen in fewer than five fractions of SABR, and large-scale randomized data is much needed. Aided by the ability to achieve necessary rectal dose constraints through placement of a rectal hydrogel, this phase II/III prospective study will, with power to establish non-inferiority, compare standard 5-fraction SABR with a novel 2-fraction regimen.

## Methods/design

### Objective

The objective of this trial is to assess the oncologic and quality of life non-inferiority of 2-fraction SABR to 27 Gy compared to 5-fraction SABR to 40 Gy, in low- and favorable intermediate-risk prostate cancer.

### Study design

This is a prospective randomized phase II/III non-inferiority control trial with pre-planned interim analyses for safety signals in the 2-fraction arm. Participating centers will be tertiary, academic hospitals in Israel (updated list available at health.gov.il) with the potential of opening additional sites (limited to the United States and Canada) over the trial period. All aspects of the trial have been approved by the relevant institutional internal review boards. Subjects will be randomized between the standard arm of prostate SABR to 40 Gy in 5 fractions and the experimental regimen of 27 Gy in 2 fractions (Fig. 1). A focal simultaneous integrated boost (SIB) to the MRI-defined dominant intraprostatic lesion (DIL) will be permitted. All patients will undergo trans-rectal ultrasound-guided placement of a radiopaque hydrogel spacer and three gold fiducial intraprostatic markers prior to simulation. Both simulation CT and a planning MRI will be used for target and normal structure delineation, though SABR delivery will not require an MRI-guided linear accelerator (LINAC).

**Fig. 1 Fig1:**
[figure not shown]
Schema of the SABR-Dual clinical trial

#### Endpoints

**Primary endpoint**.

Freedom from disease progression (FFDP), defined as clinical failure or biochemical failure per the Phoenix definition [20].

**Secondary endpoints**.

Progression free survival (PFS), defined as biochemical failure, clinical failure, or death from any cause.Distant metastasis free survival [21].Prostate cancer specific survival (PCSS).Longitudinal PSA response.Time to salvage treatment.Physician-reported GU/GI toxicity at 1, 3, 6, 9, 12, 18, 24-months (CTCAE).Patient-reported GU/GI toxicity at 1, 3, 6, 9, 12, 18, 24-months (IPSS, EPIC, SHIM).

#### Patient selection

**Inclusion criteria**.

Male patients ≥ 18 years.Diagnosis of low- or favorable intermediate-risk prostate adenocarcinoma.
T1-T2cPSA < 20Gleason 6 or 7 (3 + 4)Cannot had multiple intermediate-risk factors consistent with unfavorable-intermediate risk disease

Prostate gland < 80 cc.IPSS < 15 (unaided by a-adrenergic inhibitor or anticholinergic drugs).

**Exclusion criteria**.

Unfavorable intermediate-risk disease and above.Chronic inflammatory bowel condition (IBD, Crohn’s disease, Sarcoidosis, Rheumatic disease).Chronic immunosuppression.Contraindications to hydrogel spacer placement.Contraindications to a prostate MRI.Any prior prostate cancer treatment.Prior pelvic radiotherapy.Previous transurethral resection of the prostate (TURP) within 12 months.Hip prosthesis.Prior use of androgen deprivation therapy (ADT).

#### Pretreatment evaluation

Patients will undergo prostate cancer diagnostic evaluation with at least a standard whole-gland sextant biopsy to establish Gleason score. MRI-guided targeted biopsy is allowed as well but comprehensive whole-gland biopsy is required. An updated staging PSA will be obtained within 1 month prior to enrollment.

All patients are required to undergo a diagnostic multiparametric MRI (mpMRI) with 3T coil to identify regions suggestive of high-grade disease and to radiographically rule out the likelihood of extra-prostatic extension and/or seminal vesicle (SV) involvement. As eligible patients will have a categorization of low-risk or favorable intermediate-risk disease, systemic staging with a CT, bone scan, and/or PSMA-PET is allowed but will not be mandated.

Prior to enrollment patients will undergo a general physical exam. Baseline urinary, sexual, and bowel symptoms will be quantified using the International Prostate Symptom Score (IPSS), Sexual Health in Men (SHIM) score, and the global quality of life measure EPIC-26.

#### Data collection

All data collected on study will be entered electronically into a customized REDCap^™^ database and monitored by representative members of the Department of Clinical Research of Davidoff Cancer Center, Rabin Medical Center. All data will be retained through final censoring and follow up period, and for an additional five years thereafter. Following initial publication of clinical outcomes, deidentified data will be made available for review upon request.

### Treatment plan

#### Consent process

Written informed consent will be obtained from all subjects prior to enrollment by the treating physician.

#### Pre-simulation

Prior to simulation, all participants will undergo peri-rectal radiopaque hydrogel spacer insertion, as well as placement of 3–4 gold fiducial markers, to displace the rectum away from the high-dose radiation field and aid in target localization, respectively. If a patient is being treated using an MR-LINAC, fiducial markers will not be required.

#### Simulation imaging and immobilization

A treatment planning CT in the supine position will be acquired no sooner than in the week following hydrogel spacer placement, with the patient set up in the same position as for daily treatments, using appropriate hip, knee, and ankle support, with slice thickness of 1–2 mm. A treatment planning MRI (3-Tesla, minimum T2w sequence) will be acquired in a best approximation of the treatment position. Patients will be instructed to begin a daily stool softer beginning 1 week prior to hydrogel placement throughout the course of SABR, and will utilize a rectal enema before CT simulation and each fraction of radiation [22].

A full bladder is required for treatment with a consistent degree of bladder fullness determined by cone-beam CT (CBCT) or pre-treatment bladder scan. An empty rectum is required, and patients will be instructed to continue use of a prescribed stool softener throughout the course of SABR and place a rectal enema prior to each fraction.

#### MRI-CT registration

MRI-CT registration with a T2w MRI sequence serving as the primary fusion sequence will consist of a prostate-to-prostate registration. Precise fusion will be aided by prostate anatomy, fiducial markers, and hydrogel spacer. Internal peer review and approval of registration quality is strongly recommended. Where MRI-based treatment delivery is available, planning may be performed based on MRI alone.

#### Treatment technologies

Patients will be treated with photon-based radiation, IMRT/VMAT techniques. Allowed photon energies are 6–10 MV. Flattening filter free delivery is allowed.

#### Target volumes and margins

Gross tumor volume (GTV) will be defined as an MRI-visible PIRADS 4–5 lesions that is concordant with biopsy results. If no such lesion is visible, a GTV will not be included.

The clinical target volume (CTV) will be defined as the entire prostate gland, including GTV, as well as 1–2 cm of the seminal vesicles (SV) in the setting of favorable intermediate-risk disease.

A planning target volume (PTV) expansion will be added to account for possible variability in daily treatment set up and internal organ motion. The PTV margin will be dictated as 5 mm circumferential except for 3 mm posterior margin in the 5-fraction arm, and a uniform 2 mm expansion in the 2-fraction arm.

#### Radiation dose

Standard arm: Radiation dose will be 40 Gy divided into five equal fractions of 8 Gy per fraction to the prostate volume. When the proximal SV is included, the PTV volume of the SV that is beyond the PTV prostate volume will be prescribed 35 Gy, 7 Gy per fraction. When present, the GTV will receive an SIB to 45 Gy.

Experimental arm: Radiation dose will be 27 Gy divided into two equal fractions of 13.5 Gy per fraction to the prostate volume. When the proximal SV is included, the PTV volume of the SV that is beyond the PTV prostate volume will be prescribed 23 Gy, 11.5 Gy per fraction. When present, the GTV will receive an SIB to 30 Gy.

#### Treatment planning

In addition to the GTV, CTV, and PTV targets described above, the following organs at risk (OARs) will be contoured: bladder and bladder wall, rectum and rectal wall, urethra (with an additional 2 mm PRV avoidance structure uniformly expanded), femoral heads, large bowel, small bowel (where relevant), penile bulb, and proximal crura [23]. It is recommended to contour the fiducial markers and radiopaque hydrogel spacer to aid in daily setup. Target coverage goals are listed in Table 1 and OAR constraint goals for the standard and experimental arms are listed in Tables 2 and 3, respectively. Dose constraints may not be exceeded under any circumstance.

**Table 1 Tab1:** Target volume goals for standard and experimental arms

Structure	Parameter (Gy)	Per protocol	Variation acceptable	Notes
PTV_4000	V40	≥ 95%		Arm 1
	V39.6	≥ 97%	≥ 95%	
	D0.03 cc*	< 107%	< 108%	
CTV_4000	V39.6	≥ 100%	≥ 99%	
PTV_3500	V35	≥ 95%		
CTV_3500	V33.95	≥ 97%	≥ 95%	
PTV_2700	V27	≥ 95%		Arm 2
	V26.73	≥ 97%	≥ 95%	
	D0.03 cc*	< 107%	< 108%	
CTV_2700	V26.73	≥ 100%	≥ 99%	
PTV_2300	V23	≥ 95%		
CTV_2300	V22.31	≥ 97%	≥ 95%	

*When a simultaneous integrated boost is prescribed, maximum allowed dose to the primary PTV (either PTV_4000 or PTV_2700) will be limited to 102% of the boost dose– D0.03cc < 45.9 Gy or D0.03cc < 30.6 Gy. There is no specific minimum required SIB coverage for GTV, when present, but minimal coverage of 95% of volume covered by 95% of dose is recommended.

**Table 2 Tab2:** Organ at risk constraints for the standard arm

Structure	Parameter (Gy)	Per protocol	Variation acceptable
Bladder	D0.03 cc	< 42 Gy	D0.5cc < 41.2 Gy
	V26	≤ 25%	
	V26	≤ 50 cc	
Rectum	D0.03 cc	< 40.8 Gy	
	D1cc	< 38.5 Gy	D2cc < 38 Gy
	V36	≤ 10%	
	V32	≤ 20%	
	V20	≤ 50%	
Rectal wall (any slice)	35% circumf.	< 39 Gy	Semi-quantitative visualization
	50% circumf.	< 24 Gy	
UrethraPRV	D0.03 cc	< 40.8 Gy	
Urethra	D0.03 cc	≤ 40 Gy	
Femoral head	V22	≤ 10 cc	
	V22	≤ 5%	
Penile bulb	D0.03 cc	< 38 Gy	
	V22	≤ 30%	
Crura	D_mean_	< 4.7 Gy	
	D_2%_	< 12 Gy	
Skin	D0.03 cc	< 25 Gy	

**Table 3 Tab3:** Organ at risk constraints for the experimental arm

Structure	Parameter (Gy)	Per protocol	Variation acceptable
Bladder	D0.03 cc	< 28.08 Gy	D0.5cc < 27.54 Gy
	V16.2	≤ 25%	
	V16.2	≤ 50 cc	
Rectum	D0.03 cc	< 27 Gy	
	D1cc	< 22.95 Gy	D2cc < 21.6 Gy
	V23	≤ 10%	
	V19	≤ 20%	
	V10	≤ 50%	
Rectal wall (any slice)	35% circumf.	< 20 Gy	Semi-quantitative visualization
	50% circumf.	< 13.5 Gy	
UrethraPRV	D0.03 cc	< 27.54 Gy	
Urethra	D0.03 cc	≤ 27 Gy	
Femoral head	V13.5	≤ 10 cc	
	V13.5	≤ 5%	
Penile bulb	D0.03 cc	< 24.3 Gy	
	V13.5	≤ 30%	
Crura	D_mean_	< 3.78 Gy	
	D_2%_	< 8.8 Gy	
Skin	D0.03 cc	< 13.5 Gy	

#### Quality assurance

Each treatment plan must be peer-reviewed by another attending radiation oncologist or at chart-review rounds, with confirmation of appropriate target coverage and OAR avoidance. Plans will also undergo a second quantitative review by a radiation physicist.

#### Treatment delivery

Radiation treatment must begin within 3 weeks after simulation. A single dose of 2 mg Dexamethasone will be given prior to each radiation treatment. A CBCT will be acquired prior to the start of each treatment and alignment to fiducial markers, hydrogel spacer, and overall PTV will be confirmed. Up to 2 mm and/or 2-degree corrections will be allowed without necessitating repeat imaging. Larger corrections will require repeat CBCT confirmation. The presence of a consistently full bladder and empty rectum will be checked. In both arms, a second CBCT will be acquired to re-confirm precise alignment after approximately half of the fractional dose is delivered (if the fraction is split into two arcs, the CBCT will be repeated in between the arcs). Real-time tracking of gold fiducials markers (where present) will also be utilized where available, in which case an additional CBCT is not necessary.

For patients not yet taking Tamsulosin, a dose of 0.4 mg will be prescribed prophylactically starting day 1 of radiation through 30 days following completion of radiation. For patients already taking 0.4 mg, the dose will be increased to 0.8 mg for the same period.

In the standard arm, fractions will be delivered every-other-day with a total treatment time of maximum two weeks. In the experimental arm, an inter-fraction interval of at least three days is required, and treatment will be completed within a maximum of seven days.

#### Patient monitoring

Baseline assessment will include PSA, quantitative urinary function (IPSS), sexual health (SHIM) score, and a global quality of life measure (EPIC-26). Follow up will occur at 1 month, 3 months, continuing at 3-month intervals through 1 year, then every 6 months from years 2–5, followed by annually thereafter. PSA will be recorded in follow up at 3, 6, 9, and 12 months in the first year, then every 6 months thereafter through five years, then annually. IPSS, SHIM and EPIC scores will be recorded during each follow up.

Adverse events (AE) will be described using the grading scales found in the revised NCI Common Terminology Criteria for Adverse Events (CTCAE), version 5.0. An AE is defined as any untoward medical occurrence associated with the use of a medical intervention, which in the context of this trial include radiopaque hydrogel spacer and fiducial marker placement, and radiation therapy. The following AEs should be assessed and recorded at each protocol mandated data collection interval: dysuria, hematuria, incontinence, urinary retention, diarrhea, rectal hemorrhage, fatigue. Full schedule of patient monitoring is summarized in Table 4.

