In contrast, in designing this trial, we intentionally selected an already established dose-fractionation from the 2-fraction radiation modality with the most substantial data, namely HDR-brachytherapy. 27 Gy given in two fractions is already known to be a highly safe and effective regimen in the setting of brachytherapy, with the downside of it comprising an invasive procedure under anesthesia performed twice. As such, of all the regimen thus far having begun to be studied, our dose in two fractions is rooted in many years of published data. A small phase II study of single-fraction SABR showed potentially similar toxicity outcomes in favorable intermediate-risk patients [14], but an instance of late high grade urethral stenosis, overall higher than expected toxicity, and a trend toward inferior PFS, supported not pursuing this method further.

A second important priority in the design of this trial is the goal of presenting a planning and treatment methodology that is reproducible and broadly generalizable. While MR-LINAC technology is emerging as an important tool with possible clinical advantages [28], it is not a widely available technology and in many instances cost-prohibitive. Adaptive radiotherapy may offer similar benefits but also shares similar limitations. For these reasons, as well as to minimize patient discomfort during and surrounding treatment, we did not include endorectal applicators or immobilizers. Given the known importance of including a PTV expansion to account for minor variations in setup to assure accuracy of treatment, we did mandate insertion of a radiopaque hydrogel spacer, which has also been demonstrated on prospective studies to decrease the risk of long-term rectal toxicity by displacing the rectum away from the high dose field [29, 30].

Our study population was carefully selected to minimize the possible confounding of external factors to the oncologic and toxicity endpoints. While one could argue that it is clinically more meaningful to study radiation developments in a higher risk population, variation in target volumes, such as whether or not to include pelvic nodes, and the impact of variable duration.

ADT, could cloud the ability to more directly conclude the relative differences strictly between different radiation therapy regimen.

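### The adverse events to be checked at every visit omit urethral stenosis/obstruction and rectal ulcer/proctitis, so between-arm rates of these diagnoses rest on unprompted recording or symptom proxies

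*Protocol article*

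**What the plan says.** The Patient monitoring section of the protocol article adopts CTCAE version 5.0 and gives a broad definition: "An AE is defined as any untoward medical occurrence associated with the use of a medical intervention". It then sets a recording rule, "The following AEs should be assessed and recorded at each protocol mandated data collection interval", followed by seven terms: "dysuria, hematuria, incontinence, urinary retention, diarrhea, rectal hemorrhage, fatigue". Nothing in the wording marks the seven as examples.

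Elsewhere the article discusses two harms that are not among them:

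- **Urethral stenosis.** In the Background account of a cited single-fraction study, "one of the 15 patients in the single-fraction arm experienced delayed grade 3 urethral stenosis". The Discussion gives three reasons for not pursuing single-fraction treatment. The first two are "an instance of late high grade urethral stenosis, overall higher than expected toxicity"; the third is a trend to worse progression-free survival.
- **Rectal ulceration.** The Background says that "recent endoscopic reports reveal notably high rates of rectal ulceration after dose-escalated SABR" and that "placement of a hydrogel spacer has been demonstrated to significantly reduce this risk". The spacer is required in both arms.

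The Analysis plan compares grade distributions, and the risk of grade 2 or 3 events, for a selected set of adverse events that it does not name.

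**The concern.** A checklist gives a usable between-arm rate because each term is asked about in every patient at every visit, and absence is recorded as well as presence. A diagnosis off the list is recorded only if someone notices it and chooses to enter it. That raises two problems for the diagnoses in question.

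First, capture may be incomplete. Losing events equally in both arms pulls the two observed rates together and lowers the chance of seeing a real difference. This matters because the Conclusion hopes to show that the shorter regimen is no worse on safety.

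Second, capture may be unequal. The article describes no masking, and 2 versus 5 treatment sessions make masking implausible. That is an inference, not a statement in the text. If clinicians look harder in one arm, unprompted recording can create or hide a difference.

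The design also treats these structures as worth protecting: Tables 2 and 3 set limits for the urethra, a margin around the urethra and the rectal wall in both arms. The checklist asks about fatigue and diarrhea but not about these injuries.

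**Working it through.** **1. List against text.**

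| Harm | Where the article raises it | On the seven-term list? | Nearest listed symptom |
|---|---|---|---|
| Urethral stenosis/urinary tract obstruction | Background (1 of 15, grade 3); Discussion | No | Urinary retention, dysuria |
| Rectal ulcer/proctitis | Background (rectal ulceration) | No | Rectal hemorrhage |

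The proxies are partial. A record of retention or bleeding shows a symptom; it is not a graded diagnosis.

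**2. What else is solicited.** Endpoints schedules physician-reported GU/GI toxicity by CTCAE at seven time points to 24 months. Patient monitoring takes IPSS, SHIM and EPIC at each follow-up. Table 4 puts adverse event assessment and physical examination in every follow-up period. The Analysis plan makes EPIC-26 the main measure of treatment-related adverse effects. None of these names stenosis or ulcer: the questionnaires give scores, and the physician endpoint names no terms.

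**3. The plan's own figure.** The only design size stated is 228 per arm, for the primary endpoint. With 90% in both arms, a margin of 0.07, one-sided alpha 0.05 and 80% power:

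n = [0.90×0.10 + 0.90×0.10] × (1.645 + 0.842)² / 0.07² = 0.18 × 6.183 / 0.0049 = 227.1, rounded up to 228.

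It reproduces. This point does not change it; 228 is used below only as a number per arm.

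**4. Does the article supply a stenosis rate?** Only 1/15 = 6.7%, from a different regimen. Its exact 95% confidence interval is about 0.2% to 32%. It fixes no planning rate.

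**5. Illustration of equal under-capture.** True rates and capture fractions are assumed. Observed rate = true rate × capture fraction. Power is by exact binomial enumeration of a two-sided Fisher test at 0.05, 228 per arm.

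| Assumed true rates | Full capture | 75% capture | 50% capture |
|---|---|---|---|
| 1% vs 5% | 64% | 47% | 25% |
| 2% vs 6.7% | 63% | 47% | 28% |

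In the first row the expected recorded counts are 228×0.01 = 2.3 vs 228×0.05 = 11.4 at full capture, and 1.1 vs 5.7 at 50%. With 251 per arm (502/2), the first row becomes 70%, 53% and 30%.

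**6. Illustration of unequal capture.** The table above applies the same capture to both arms, so it says nothing about differential recording. For that, assume a true rate of 4% in both arms, captured at 50% in one and 80% in the other. The observed rates are 0.04×0.5 = 2.0% and 0.04×0.8 = 3.2%, an apparent relative risk of 1.6 where the true value is 1. The direction could be either way.

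**The case against.** The strongest reply has four parts.

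**Safety is assessed far more widely than by this list.** This stands. A reader might infer that the trial's key safety comparison relies on unsolicited reports. The documents do not support that: EPIC-26, IPSS, scheduled GU/GI grading and the listed symptoms are all solicited. In addition, the monitoring committee reviews any reported grade 3 to 5 toxicity, whatever the term. Only diagnosis-level capture of these harms is unprompted. The committee route, however, starts from a report and does not reach grade 2.

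**The article does not call these harms the main risks of two-fraction treatment.** This also stands. Stenosis is one patient in a cited single-fraction arm. Ulceration is tied to dose escalation, not to fewer fractions, and is said to be reduced by a spacer that both arms receive. Nothing shows that these are the events most likely to separate the arms.

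**A tick-box cannot find an asymptomatic ulcer.** Correct. The cited ulcer findings are endoscopic and the trial schedules no endoscopy. The change reaches only symptomatic or clinically diagnosed events.

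**This is a condensed article, and the full list may sit in the protocol or case report form.** This would answer a complaint about silence. Here the article states a list, and words it as the set to be recorded at each interval. A longer form may exist; if so, the article's list should be brought into line with it.

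**Conclusion.** The point holds at a limited size. The stated visit checklist is poorly matched to harms that the article itself raises. Between-arm rates of urethral stenosis/obstruction and of rectal ulcer/proctitis would rest on unprompted recording or on symptom proxies, which may be incomplete and may differ by arm.

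The size of any loss or bias cannot be derived from the documents. The power figures depend wholly on assumed rates and capture fractions. Even full capture leaves about 64% power in the illustration, for comparisons that the plan already calls unpowered. The possibility of differential recording rests on the inference that treatment is not masked. The primary endpoint and its sample size are unaffected.

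**What to change.** In Patient monitoring, add two graded CTCAE v5.0 entries to the adverse events recorded at every existing visit in both arms: urethral stenosis/urinary tract obstruction, and symptomatic or clinically diagnosed rectal ulcer/proctitis. Record grade 0 when absent, so that the denominators are known. In the Analysis plan, name both among the adverse events selected for comparison.

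The cost is a few more form fields and a few more unpowered comparisons. No visit, procedure or endoscopy is added, and treatment does not change. Reports should say that asymptomatic ulcers are not ascertained.
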